To address the need for change at two levels—organizational and service delivery system—to increase the intent and ability of primary care providers to identify and treat opioid and alcohol use disorders (OAUD), we designed a multi-level study to create and evaluate change at both levels. We call this study substance use motivation medication integrated treatment (SUMMIT) and focus on alcohol and opiate use disorders because of their relevance to the clinic population and availability of effective medications. At the organizational level, we test the effects of an organizational readiness intervention on the organization’s readiness to identify and treat individuals with opioid and alcohol use disorders. At the service delivery system level, we use Wagner’s Chronic Care Model [34] to reorganize and guide how care for OAUD is provided and supported; we call the service delivery intervention integrated collaborative care (ICC). Integrated, collaborative approaches have been successful in improving outcomes for patients experiencing a variety of different chronic illnesses, including diabetes [35], asthma [35], and depression [36]. ICC has improved implementation of evidence-based treatments and quality of care [37], lowered costs [38], improved patient outcomes [39-42], and is thought to be feasible for and sustainable in primary care clinics [43]. We test the effects of the organizational readiness intervention using a repeated measures pre-post design and the impact of the service delivery intervention on patient-level outcomes using a randomized controlled trial (RCT) to compare the service delivery intervention (ICC) with “service as usual” (SAU) on service system and patient outcomes. We hypothesize that provider (providers include administrators, medical and mental health providers, and other staff) readiness to implement the EBP and patient-centered SUD care will improve from the pre-organizational readiness intervention period (year 1) to the post-readiness intervention periods (years 2–5); that patients in the ICC condition will report more integrated, patient-centered evidence-based care for their opioid and/or alcohol use disorders, will be more likely to receive OAUD care, and will have lower overall health care utilization (e.g., emergency department and medical visits) than patients in the SAU condition; and that provider adoption of EBP will increase from year 2 to years 3 and 4 and that providers will still be delivering OAUD EBP a year after completion of the study in year 5. We also hypothesize that patients in the ICC condition will report less substance use, fewer SUD consequences, higher health and mental health functioning, and greater satisfaction with their SUD care 6 months after enrollment than SAU patients.

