### Study design

The study is designed to test the combined effect of both an organizational readiness intervention (which includes a 1-year organizational preparation period and an 8-month pilot of the ICC condition study) and a service delivery intervention (see Figure 2). We examine the effects of the interventions on organizational readiness, service system, and patient outcomes, all of which are believed to be important in understanding the uptake of new practices [58]. To test the unique effects of the organizational readiness intervention on provider outcomes, we use a pre-post-intervention design and measure these outcomes at the beginning of the study and then again at the end of year 1. At the end of year 1, we implement an eight-month pilot test of ICC. During the pilot test, providers gain experience with the protocols, and the protocols are iteratively adapted and refined based on provider feedback. Because we hypothesize that readiness outcomes may continue to improve as providers gain experience with ICC and the three treatments, we continue to measure organizational readiness outcomes annually at years 2–5. Thus, changes in outcomes between year 1 and years 2–5 reflect the combined effect of both the organizational readiness intervention and ICC on provider outcomes. To test the effects of the interventions on service system and patient-level outcomes, we are conducting an RCT to compare the effects of ICC with SAU. Service-system outcomes are patient-centered collaborative care, utilization of SUD treatment, patient utilization of health care services, provider adoption of EBP, and sustainability of EBP. Patient-level outcomes include substance use, consequences of use, physical and mental health functioning, and patient satisfaction with SUD care.

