### Study participants

#### Organizational readiness intervention

Organizational readiness intervention participants are full-time clinic administrators, medical and mental health providers, and other clinic staff, including medical assistants, discharge coordinators, and front desk and security staff who agree to participate in interviews, focus groups and/or surveys (*N* = 70).

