#### Organizational readiness intervention

##### Procedures

We use qualitative and quantitative methods to study our organizational readiness outcomes as follows: 1) *Provider focus groups and semi-structured interviews*. We conduct focus groups with medical and mental health providers and one-on-one interviews with key administrators to inform the development of our intervention and EBP protocols and to understand perceptions of acceptability, appropriateness, feasibility, and intention to adopt the ICC and EBP protocols. For both the focus groups and the interviews, we follow a semi-structured protocol guide that asks “grand tour” questions related to each domain (i.e., general thoughts about ICC and the EBP), and includes specific probes for more detailed responses. 2) *Provider Surveys*. We also conduct surveys in years 1–5 with all the staff and providers to assess changes in organizational readiness outcomes throughout the study. The survey includes validated measures as well as “home-grown” items about specific activities, such as whether providers prescribed a medication and any barriers to doing so. Surveys are web-based, or, for providers with less access to email, through in-person, paper and pencil surveys.

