
##### Analysis plan

The semi-structured interview and focus group data will be analyzed to identify key facilitators and barriers to implementation using classic content analyses. Our quantitative analysis of survey items will consist of pre-post, one-way repeated measures ANOVA comparisons of survey responses between pre- and all post-intervention periods.

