##### Analysis plan

Our quantitative analysis of provider survey items and administrative data related to service system outcomes will consist of pre-post, one-way repeated measures ANOVA comparisons of survey responses between pre- and all post-intervention periods. To analyze patient-level outcomes, we use an intent-to-treat approach. We will first conduct a bivariate analysis to estimate the uncontrolled association between being in the ICC group and outcome. In addition, even though our design randomly assigns patients, we will assess any possible imbalance in covariates between ICC and SAU groups including age, gender, race/ethnicity, and education that affect the impact of the ICC intervention on the outcomes. In cases where observed imbalances are attributable to sample attrition, we will correct for potential bias due to attrition at follow-up using response weights. In addition, characteristics related to an outcome at a conservative significance level of α = 0.2 will be considered covariates in a multivariate analysis for reduction of bias if imbalanced or for efficiency gains. For the multivariate analyses, we will infer about the impact of ICC on an outcome by fitting hierarchical models using SAS Proc Mixed, R LME4, and Winbugs. These models take into account the multi-level structure of the data: two repeated measures over time (baseline and 6 months) nested within patient and patients nested within clinics. Sensitivity analyses will be conducted testing model functional forms, the covariates to be used, and the impact of influential outliers in the analyses results. For outcomes assessed only at month 6 (e.g., treatment satisfaction), we will use cross-sectional analyses (such as linear and logistic regression) to estimate the effect of ICC relative to SAU. This study was designed to estimate sufficient effect sizes that can be detected with a power of at least 80% when comparing the outcomes of patients randomly assigned to the two conditions in an end-status analysis at month 6 for a 5% significance level. For continuous outcomes, the study will be able to detect effect sizes of about 0.30–0.32 standard deviations. These are the kind of effects that can be expected for an intervention like ICC [42]. For dichotomous outcomes, we will be able to detect a difference of 13–14 percentage points under the assumption that the SAU group has a 15% rate of receiving the outcome.

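### One-way repeated measures ANOVA suits five or six staff survey waves poorly: with its usual pooled error and lag-decaying correlation, it is liberal for long-run change and conservative for the first-year change

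*Protocol article*

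**What the plan says.** The Analysis plan under Organizational readiness intervention gives the quantitative analysis of survey items as pre-post comparisons by "one-way repeated measures ANOVA comparisons of survey responses between pre- and all post-intervention periods". The Analysis plan under Service delivery intervention repeats those words for provider survey items and for administrative data on service system outcomes. No other quantitative test is named for the staff surveys.

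On timing, Procedures (Organizational readiness intervention) states "We also conduct surveys in years 1–5 with all the staff and providers". Study design says that, to isolate the effect of the readiness intervention on providers, the investigators "measure these outcomes at the beginning of the study and then again at the end of year 1", and then that "we continue to measure organizational readiness outcomes annually at years 2–5". This makes five waves if year 1 counts once and six if both year-1 measurements count. The hypothesis in Background is improvement from year 1, taken as the pre period, to years 2 to 5. Study participants gives 70 staff.

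The only significance level in the article belongs to the patient comparison, "in an end-status analysis at month 6 for a 5% significance level". The staff survey analysis has none, and no correlation, variance, contrast coding or error term is given for it.

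**The concern.** The classical one-way repeated measures ANOVA has a single error mean square, staff by wave. It is right for every contrast only if all differences between waves have the same variance (sphericity). In annual surveys over five years, answers one year apart may well be more alike than answers four or five years apart. The pre wave also sits at one end of the series. Its differences from later waves would then have more variance than the pooled average, and its difference from the next wave would have less.

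Two conclusions are at stake. The long-run hypothesis (year 1 against years 2 to 5) would be tested with a standard error that is too small. The comparison that Study design reserves for the readiness intervention alone (start against end of year 1) would be tested with one that is too large. Neither problem depends on missing surveys: both occur with full response.

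**Working it through.** **Plan's own figure.** The article gives no error rate, power or sample-size calculation for this analysis, so there is nothing to reproduce.

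**Inputs from the article.** k = 5 or 6 waves; n = 70 staff; contrast pre versus all post periods.

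**Assumptions.** Two-sided nominal 5%; equal variances (set to 1); equally spaced waves; correlation ρ^lag with ρ = 0.5 to 0.9; pooled error used for contrasts. A constant person effect cancels and does not alter the results.

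**Formulae.** Expected pooled mean square: MSE = mean variance − mean covariance. For a contrast c and covariance matrix S, the variance ratio is VR = c'Sc / (c'c × MSE). Actual two-sided error = 2[1 − Φ(1.96/√VR)].

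**Worked case, k = 6, ρ = 0.8.**
- Mean pairwise correlation = (5×0.8 + 4×0.64 + 3×0.512 + 2×0.4096 + 0.3277)/15 = 0.616, so MSE = 0.384.
- Pre versus mean of five post waves: true variance = 1 + 0.724 − 2×0.538 = 0.649; pooled = 1.2×0.384 = 0.461; VR = 1.41; error 9.9%.
- Pre versus last wave: true = 2(1 − 0.3277) = 1.345; pooled = 2×0.384 = 0.768; VR = 1.75; error 13.9%.
- Pre versus next wave (start versus end of year 1): true = 2(1 − 0.8) = 0.400; pooled = 0.768; VR = 0.52; error 0.7%.

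**Across the assumed range (actual two-sided error, %).**

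| Waves | ρ | Pre v mean post | Pre v last wave | Pre v next wave |
|---|---|---|---|---|
| 5 | 0.5 | 7.4 | 9.2 | 2.1 |
| 5 | 0.7 | 8.8 | 11.9 | 1.3 |
| 5 | 0.8 | 9.5 | 13.4 | 1.0 |
| 5 | 0.9 | 10.2 | 15.0 | 0.8 |
| 6 | 0.5 | 7.4 | 8.9 | 1.8 |
| 6 | 0.7 | 9.0 | 12.0 | 1.0 |
| 6 | 0.8 | 9.9 | 13.9 | 0.7 |
| 6 | 0.9 | 10.8 | 15.9 | 0.4 |

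**Simulation, n = 70, same assumptions (8,000 runs per setting).** The uncorrected omnibus F rejects in 6.4–8.9% of runs, within a band of about 6–10% once simulation error is allowed for. Pre versus mean of post agrees with the table. Rejections in the direction of improvement are about half: 7.4–10.8% halves to 3.7–5.4%, against 2.5%.

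**Other covariance assumptions, pre versus mean of post.**
- Independent measurement noise of 0.5 to 1 times the autoregressive variance: about 6–7%. Pre versus last wave becomes about 6.6–8.9%.
- Compound symmetry: VR = 1, error 5.0%.
- Compound symmetry with pre variance 0.7–0.8 times post: about 3–4%, conservative.
- Pre and post coded as a two-level factor: exactly 5%.

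**After the fix.** With a paired error specific to the contrast, simulated error was 4.5–5.6% in every setting tried. A Greenhouse–Geisser omnibus test gave 4.2–5.3%.

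**The case against.** The strongest reply is that the article does not say a pooled error is used for contrasts. It does not rule out a sphericity correction or paired contrasts, and a condensed article may leave such details to an analysis plan that is not shown. A two-level pre/post factor would hold 5%. That stands, and it is why every figure here is conditional. It does not remove the point: the article names a specific method in two places, and the default form of that method fits this series of waves badly. This is a stated choice, not an omission.

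A reader might infer that readiness would be falsely declared improved 8–16% of the time. The documents do not support that. The hypothesis contrast is pre versus all post, for which the range is about 7–11%; the 16% end belongs to the single pair pre versus last wave at ρ = 0.9. These rates are two-sided, so false improvement is about half. The 5% level is itself an assumption for this analysis. Measurement noise, which survey scales usually carry, brings the figure to about 6–7%.

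Nor is the method liberal throughout. For start versus end of year 1 it is conservative. And readiness does not rest on this test alone: focus groups, interviews and finished adapted protocols also count, though the ANOVA is the only quantitative test named for the survey items.

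**Conclusion.** The concern holds in conditional form. If correlation falls with lag as assumed and the pooled error is used for contrasts, one error term serves neither of the study's two provider questions: it is moderately liberal for long-run change and clearly conservative for the first-year change. The inflation shrinks with measurement noise and vanishes under compound symmetry, and the article gives nothing from which to choose between these cases. Because the direction of the error depends on the contrast and on an unknown covariance, the method should not rely on sphericity. The point is worth correcting because the remedy is cheap; it does not show that the survey conclusions will be wrong. The randomised comparison of patients is not affected.

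**What to change.** In both Analysis plan paragraphs, replace the one-way repeated measures ANOVA of the staff surveys by a mixed model for repeated measures, with survey wave as a factor and an unstructured within-person covariance. Prespecify the contrasts (start versus end of year 1; pre versus mean of post; pre versus each later year), and test each with its own standard error and small-sample degrees of freedom. State the significance level and whether there are five or six waves. An unstructured matrix has k(k+1)/2 parameters, 15 or 21 here, which 70 staff can support if response is adequate.

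If ANOVA is kept, use a paired test on each person's contrast and an epsilon-corrected omnibus test. The epsilon correction alone does not repair contrasts that still use the pooled error. If the full analysis plan already does this, confirming it is enough.

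The cost is wording only. No new data are needed, and the plan already uses hierarchical models for patients. Under the assumed correlations the standard error, and so the interval, changes by the factor √VR: about 10–22% wider for pre versus mean of post (√1.21 to √1.49), about 15–39% wider for pre versus last wave (√1.32 to √1.94), and about 15–31% narrower for start versus end of year 1 (√0.72 to √0.47).

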#### Service delivery intervention

To examine the effect of our service delivery intervention, we examine service system and patient functioning outcomes.

##### Procedures

We use a combination of administrative records, patient interviews and staff surveys to evaluate service system and patient outcomes, as follows: 1) *Administrative records*. We collect three administrative files every 6 months—appointments (all appointments scheduled whether or not they were kept), encounters (including medical and therapy visit reasons and diagnoses), and medication orders. 2) *Patient interviews*. The patient interview contains an assessment of SUD diagnoses, substance use frequency and quantity, consequences related to use, and health and mental health functioning items. We administer patient interviews at baseline and 6 months after enrollment. 3) *Staff surveys*. Staff surveys are described above.

##### Service system measures

We are analyzing five service system outcomes: (1) *Patient-centered, collaborative SUD care*. We measure patient experiences using a locally developed measure based on the validated Patient Assessment of Chronic Illness Care (PACIC) [73]. Provider perceptions of collaborative SUD care are measured using the Assessment of Chronic Illness Care (ACIC) [74]. (2) *Patient utilization of SUD services*. This refers to patient linkage to and usage of appropriate treatment. We measure this by examining clinic administrative records that capture all patient encounter dates, types and providers, and by patient self-report of clinic services on the follow-up survey. (3) *Patient utilization of health care services*. This refers to utilization of emergency department and health care services. We measure this by examining clinic administrative records of clinic health care visits and by patient self-report of emergency department visits. (4) *Provider adoption of EBP*. This is a measure of provider use of the EBP (either of the medications or the brief therapy). Although adoption is sometimes thought of as an implementation (or readiness) outcome, we include it with service system outcomes because we believe that both interventions—organizational readiness and service delivery—are needed for adoption of EBP. We measure adoption by examining administrative records for prescription of either medication or use of the therapy and by asking providers to self-report use of the EBP in the survey. (5) *Sustainability of EBP*. This is the extent to which the three EBP are still being utilized during year 5 of the study. Following the end of patient enrollment in the RCT, we will continue to monitor clinic practices to examine whether the EBPs are still being utilized following the end of the RCT.

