## Methods/design

### Study setting

We are conducting the study in a large urban, federally qualified health center (FQHC) in Los Angeles that serves approximately 20,000 patients annually. The study is taking place at the FQHC’s two largest sites. We elected to hold the study in an FQHC because of the expected influx of patients into publicly funded clinics due to expanded coverage, an increased funding and an increase in the number of clinics due to the Patient Protection and Affordable Care Act (PPACA) [57], and the greater opportunity to reach more individuals who need treatment. The clinic currently has integrated mental health services and provides treatment for anxiety and depressive disorders; however, prior to the study, the clinic did not conduct any screening or treatment for SUD. If substance misuse was identified, patients were sometimes, but not systematically, referred to specialty care.

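### Use of SUD treatment is measured only inside the clinic, although its definition and hypothesis carry no site limit; outside treatment would be scored as none, probably more often in SAU

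*Protocol article*

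**What the plan says.** The Background section gives the hypothesis for ICC patients relative to SAU patients: they "will be more likely to receive OAUD care, and will have lower overall health care utilization (e.g., emergency department and medical visits" and so on. No place of care is attached to the first part.

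Under Service system measures, the second outcome is patient utilization of SUD services. Its definition is also free of site: "This refers to patient linkage to and usage of appropriate treatment". Two sources follow. The first is the clinic's own files: "We measure this by examining clinic administrative records that capture all patient encounter dates, types and providers". The second is the patient interview, but only for the clinic's services: "by patient self-report of clinic services on the follow-up survey".

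The Study setting section describes care before the trial: "prior to the study, the clinic did not conduct any screening or treatment for SUD". Where misuse was identified, "patients were sometimes, but not systematically, referred to specialty care".

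The Service delivery intervention section describes ICC as a reorganisation of the clinic's own delivery system around the evidence-based practices. One of its five components is building links with community resources.

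**The concern.** What is to be claimed (receipt of appropriate treatment) is wider than what is observed (treatment at this FQHC). A gap of this kind is harmless to the arm comparison only if the treatment missed is equally common in both arms. Here there is reason to expect otherwise. ICC is built to deliver medication and therapy in the clinic, while the only treatment route described for the clinic's patients before the trial ran through outside specialty care. An SAU patient who is referred out and treated would be recorded as untreated.

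Randomisation does not protect against this, because the error arises from where care is delivered after assignment. Covariate adjustment, response weights and the sensitivity analyses on model form, covariates and outliers in the Analysis plan do not address it either. At stake is whether a positive result means that more patients were treated, or partly that treatment moved to a place where the trial could see it.

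**Working it through.** **The plan's own figure, for scale.** The Analysis plan states at least 80% power at the 5% level for 13 to 14 points against a 15% SAU rate, and for 0.30 to 0.32 SD. I assume a two-sided test and 1:1 allocation.

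- Proportions: n per arm = [1.96·√(2p̄q̄) + 0.842·√(p₁q₁ + p₂q₂)]² / d². For d = 0.13 this is 156 and for d = 0.14 it is 137.
- Means: n per arm = 2(1.96 + 0.842)² / d². For d = 0.30 this is 175 and for d = 0.32 it is 154.

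These imply roughly 270 to 350 analysed patients out of 400, which is consistent with loss to follow-up. The figure is not in dispute. It is a generic detectable difference for any dichotomous outcome, not an expected effect on treatment receipt.

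**The artefact.** Let p be the true proportion treated anywhere in an arm, and f the share of those treated only outside the clinic. The observed proportion is p(1 − f). Hence:

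observed difference − true difference = p_SAU·f_SAU − p_ICC·f_ICC

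The documents give neither f. What follows is an illustration under assumptions.

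*No true effect, p = 15% in both arms (borrowed from the Analysis plan), ICC fully captured (f_ICC = 0):*

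| f_SAU | False difference | Chance of a significant result favouring ICC, 160 per arm | Same, 200 per arm |
|---|---|---|---|
| 25% | 0.15 × 0.25 = 3.8 points | 17% | 20% |
| 50% | 0.15 × 0.50 = 7.5 points | 57% | 66% |
| 75% | 0.15 × 0.75 = 11.2 points | 94% | 97% |

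The nominal chance in that direction is 2.5%.

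*The same, but 25% of treated ICC patients also treated only outside:* the false differences become 0.15 × (0.25 − 0.25) = 0, then 0.15 × 0.25 = 3.7 and 0.15 × 0.50 = 7.5 points.

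*A lower base rate.* The Background's national figures (22.7 million needing treatment, 20.2 million not receiving it) give 2.5/22.7 = 11% treated. That is a different population. With p = 11% and f_ICC = 0, the false differences are 2.8, 5.5 and 8.3 points.

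*Direction is not guaranteed.* If ICC truly raises treatment to 29% against 15%, and the outside-only share is 25% in both arms, the error is 0.15 × 0.25 − 0.29 × 0.25 = −3.5 points. The observed difference is then 10.5 instead of 14 points, an error against ICC.

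**The case against.** **The direction may be overstated.** Referral was occasional, it is described for the period before the study, and patients already in SUD treatment are excluded. ICC's community links may themselves send patients to outside treatment. All of this stands. It makes the size unknown and the direction probable, not certain. It does not make the two sources see outside care.

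**In-clinic treatment is a legitimate outcome.** The Abstract frames the aim as uptake of SUD treatment in primary care. This stands too, and it is why renaming the outcome is an acceptable minimum. As written, however, the definition and the hypothesis claim more than that.

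**The interview may already ask about outside treatment.** The instrument is not shown, and the content list under Procedures leaves out items that are described elsewhere, such as emergency department visits. That is possible. But the article does specify this source, and limits it to clinic services. If a wider item exists, the fix is simply to say so and use it.

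**A stronger reading.** A reader might infer that the health care utilization outcome is biased in the same way, because ICC's therapy and medication visits are clinic encounters and would inflate the count that ICC is predicted to lower. The documents do not support this. That outcome does not rest on clinic files alone: "We measure this by examining clinic administrative records of clinic health care visits and by patient self-report of emergency department visits". SUD services and health care services are listed as separate outcomes, and the text neither includes nor excludes ICC treatment visits in the second. The encounter file holds visit reasons and diagnoses, so the visits can be separated. Counting them could even be the right answer to a hypothesis about overall utilization.

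**Conclusion.** The point holds for the SUD-utilization outcome only. Followed as written, the measure scores treatment received outside the FQHC as no treatment, while the definition and hypothesis concern treatment received anywhere. Because the described pre-study route was outside referral and ICC treats in the clinic, the loss is probably greater in SAU and would then favour ICC.

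Its size cannot be derived from the documents. The illustrated 4 to 11 points rest on an assumed 15% true rate in both arms, full capture in ICC, and 25% to 75% of treated SAU patients being treated only outside. The figure shrinks as ICC patients also use outside care, and the error can reverse when ICC raises treatment substantially. The illustration shows that the artefact could be a sizeable part of the 13 to 14 points that the trial can detect, not that it is.

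**What to change.** Add to the 6-month telephone interview, in both arms and with identical wording, an item on SUD treatment from any provider since baseline. Report any-source treatment and in-clinic treatment as two separate results, and tie the Background hypothesis to the any-source one.

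The cost is an interview item and incomplete coverage. The Trial status section places the trial in month 11 of 18, so patients enrolled in about the first 5 months had already passed their 6-month interview. With even accrual that is 5/18 = 28% if all 18 months are enrolment, and up to 5/12 = 42% if the 18 months include the 6-month follow-up. The any-source result would be limited to patients who were asked the item, and should be labelled so. Outside treatment of the earlier patients cannot be recovered from clinic files.

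If no item can be added, the minimum is to name the outcome SUD treatment received at the clinic, narrow the hypothesis and the conclusion to match, and list unobserved outside treatment among the limitations. That costs only wording.
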